### **3.3 Risk / Benefit Conclusion**

Pre-clinical findings indicate that the Mg based scaffold is less thrombogenic, provokes less inflammatory response and reduces formation of new atherosclerosis when compared to other available scaffolds and DES which eventually results in improved endothelial integrity. Available data on DREAMS 2G on more than 1000 subjects with a low rate of target lesion failure and scaffold thrombosis further support these beneficial findings and show that the device is safe and efficient when used according to the instructions of use.

The iterations of the device from DREAMS 2G to DREAMS 3G have addressed potential disadvantages of DREAMS 2G while maintaining the characteristic features that are thought to be responsible for the beneficial pre-clinical and clinical findings. This FIM trial will provide further evidence of the safe use of bioresorbable Mg based scaffolds in the treatment of coronary artery lesions. The device will be used under controlled conditions and subjects will be closely monitored. Every precaution has been taken to protect the health and safety of the subjects.

Moreover, subjects will be closely monitored throughout the clinical investigation duration. They will be evaluated at pre-determined time points to assess their clinical status and follow-up angiographies (including additional imaging by IVUS and OCT) will be performed to assess the status of both target lesion and the scaffold.

An independent Data Monitoring Committee (DMC) will monitor safety throughout the clinical investigation. Stopping rules will be discussed with the DMC and applied for subject safety throughout enrollment.

Therefore we conclude that the benefits of the new DREAMS 3G device outweigh the risks that are involved within this study.

## 4. CLINICAL INVESTIGATION

### 4.1 Study Objectives

The study objective is the assessment of safety and clinical performance of the DREAMS 3G in de novo coronary artery lesion and in order to obtain CE-approval.

### 4.2 Hypothesis

As a primary endpoint, the BIOMAG-I trial will assess non-inferiority of the 6-month in-scaffold late lumen loss of the DREAMS 3G scaffold vs. in-scaffold late lumen loss of a historical control from clinical trials with PLLA scaffolds as well as metallic scaffolds.

| Scaffold | 6 months
In-scaffold LLL (mm)
Mean ( SD) | N | Publication |
|-----------------|---------------------------------------------------------|----------|--------------------|
| ABSORB   | 0.44(0.35)                                              | 26       | Ormiston 2008 (46) |
| ABSORB   | 0.19(0.18)                                              | 41       | Serruys 2010 (37)  |
| Desolve  | 0.19(0.19)                                              | 14       | Verheye 2014 (94)  |
| Magmaris | 0.44(0.36)                                              | 113      | Haude 2016 (11)    |
| Desolve  | 0.20(0.32)                                              | 113      | Abizaid 2016 (70)  |

| Scaffold  | 6 months             | N   | Publication          |
|-----------|----------------------|-----|----------------------|
|           | In-scaffold LLL (mm) |     |                      |
|           | Mean ( SD)           |     |                      |
| Fantom II | 0.25(0.4)            | 100 | Chevalier 2019 (102) |

### 4.3 Relevance of the trial in the context to the state of the art of clinical practice

This trial will provide further information on the efficacy and safety of a novel drug eluting absorbable Mg based scaffold. State of the art technologies (coronary angiography, OCT and IVUS) will be applied to evaluate the physiological healing process at the lesion site.

### 4.4 Study Design

This is a prospective, multi-center and single arm first-in-man trial that will be conducted in up to 15 investigational study sites.

It will enrol up to 115 subjects (including an estimated drop-out rate of 25% at 12 months follow up). Clinical follow up visits will take place at 1, 6, and 12 months and annually thereafter until 36 months post procedure.

Subjects will undergo an angiographic follow up (including OCT and IVUS) at 6 months and at 12 months post-procedure.

If subjects consent, vasomotion will be assessed angiographically with acetylcholine followed by nitroglycerine at 12 months follow up.

Information on previous clinical investigations with predecessors of the device can be found in section 1.1. Concomitant medication guidelines are described in section 5.7.

#### 4.5 Study population

The study population will consist of subjects with de novo coronary artery lesions who suffer from symptomatic coronary artery disease and who need a percutaneous coronary intervention (PCI). Only subjects with up to 2 single lesions in 2 separate vessels will be included.

#### 4.6 Study Duration

The anticipated duration of this clinical investigation is approximately 3.5 years (First Subject In until Last Subject Out):

Enrolment duration: approximately 15 months

Follow up phase: 3 years

#### 4.7 Primary Endpoint

The primary endpoint is in-scaffold late lumen loss (LLL) at 6-month post-procedure. Late lumen loss is the most commonly used surrogate efficacy endpoint in coronary artery disease. The angiographic assessment of late lumen loss reflects the efficacy of the device independent of inter-subject variations of vessel diameters (117,118).

The DREAMS 3G starts to lose its mechanical integrity between 3 and 6 months and thus does not have any scaffolding properties after 6-month, which is the reason for choosing 6-month LLL as the primary endpoint. Additionally the DREAMS 3G should be fully absorbed at approximately 12 months post procedure, therefore an angiographic examination at 12 months is planned to assess LLL, % diameter stenosis and binary restenosis rate to further support the assessment of the efficacy and safety of the DREAMS 3G device.

#### 4.8 Secondary Endpoints

##### Clinical

- Target Lesion Failure (TLF\*) at 1, 6, 12, and annually up to 36 months follow up

- Cardiac death at 1, 6, 12, and annually up to 36 months follow up (according to ARC-1 definition)
- Target vessel MI at 1, 6, 12, and annually up to 36 months follow up\*\*
- Clinically driven target lesion revascularization at 1, 6, 12, and annually up to 36 months follow up
- Clinically driven target vessel revascularization at 1, 6, 12, and annually up to 36 months follow up
- Definite and probable scaffold thrombosis rate at at 1, 6, 12, and annually up to 36 months follow up (according to ARC-2 definition)
- Procedure success: achievement of a final diameter stenosis of <30% by QCA, using any percutaneous method, without the occurrence of death, Q-wave or non-Q-wave MI, or repeat revascularization of the target lesion during the hospital stay.
- Device Success: final residual diameter stenosis of <30% by QCA, or visual assessment using the assigned device only with:
  - Successful delivery of the scaffold to the target lesion
  - Appropriate scaffold deployment
  - Successful removal of the delivery system

\*defined according to ARC-2 and ARC-1 definition.

\*\* periprocedural MIs will be adjudicated according to SCAI-definitions and ARC-2 definitions

Secondary clinical endpoints were selected as per recommendations of the American College of Cardiology (ACC) and the American Heart Association (AHA) (Ref. ACC/AHA CLINICAL DATA STANDARDS: "", JACC VOL2014 ACC/AHA Key Data Elements and Definitions for Cardiovascular Endpoint Events in Clinical Trials. 66, NO. 4, 2015) (119).

### Angiographic

- In-segment late lumen loss at 6 months
- In-scaffold and in-segment late lumen loss at 12 months
- Binary in-scaffold and in-segment restenosis rate at 6 and 12 months
- % in-scaffold and in-segment diameter stenosis at 6 and 12 months

## **OCT and IVUS**

Descriptive analysis of vessel morphology, lesion composition and scaffold strut data

## **Vasomotion**

Descriptive analysis of vessel movement

### **4.9 Inclusion Criteria**

1. Subject is  $\geq 18$  years and  $\leq 80$  years of age
2. Written subject informed consent available prior to PCI
3. Subject eligible for PCI according to the 2018 ESC/EACTS Guidelines on myocardial revascularization (72)
4. Subjects with a maximum of two single lesions in two separate coronary arteries which have to be de novo lesions and can be covered with 1 device each
5. Reference vessel diameter between 2.5-4.2 mm by visual estimation, depending on the scaffold size used
6. Target lesion length  $\leq 28$  mm by visual estimation, depending on the scaffold size used
7. Target lesion stenosis by visual estimation  $\geq 50\%$  -  $< 100\%$  and TIMI flow  $\geq 1$  (assisted by e.g. QCA / IVUS /FFR).
8. Subjects with stable or unstable angina pectoris or documented silent ischemia or hemodynamically stable NSTEMI patients without angiographic evidence of thrombus at target lesion
9. NOTE: patient with acute STEMI can not be included in the study (according to exclusion criteria 2) Subject who has no contraindication for Dual Anti Platelet Therapy (DAPT)

### **4.10 Exclusion Criteria**

1. Pregnant or breast-feeding females or females who intend to become pregnant during the time of the study.

2. Subject has clinical symptoms and electrocardiogram (ECG) changes consistent with acute ST elevation myocardial infarction (STEMI) within 72 hours prior to the index procedure.

NOTE: after 72 hours, any lesion other than the one causing the acute STEMI (culprit lesion) in any other epicardial vessel, may be treated according to the inclusion and exclusion criteria

Left main coronary artery disease

3. Left main coronary artery disease
4. Three-vessels with coronary artery disease requiring treatment at time of procedure, including: left main, left anterior descending artery (LAD) right coronary artery (RCA) and circumflex coronary artery (Cx)
5. Planned interventional treatment of any non-target vessel within 12-month post-procedure
6. Subjects on dialysis
7. Impaired renal function (serum creatinine > 2.5 mg/dl or 221 µmol/l, determined within 72 hours prior to intervention)
8. Planned future intervention of a second lesion within the target vessel.
9. Ostial target lesion (within 5.0 mm of vessel origin)
10. Target lesion involves a side branch >2.0 mm in diameter
11. Documented left ventricular ejection fraction (LVEF) ≤ 30% within the last 6 months
12. Heavily calcified lesion which can not be adequately pre-dilated by a non-compliant and/ or scoring balloon as described in exclusion criteria 15.
13. Target lesion is located in or supplied by an arterial or venous bypass graft.

14. Target lesion requiring treatment with a device other than the non-compliant pre-dilatation balloon or scoring balloon prior to scaffold placement (including but not limited to rotational atherectomy, etc.).
15. Unsuccessful pre-dilatation, defined as a residual stenosis rate more than 20%, estimated by any method and / or angiographic complications (e.g. distal embolization, side branch closure, extensive dissections).
16. Known allergies or intolerances to: Acetylsalicylic Acid (ASA), P2Y12 inhibitors, Heparin, Contrast medium, Sirolimus, or similar drugs; or the scaffold material (Magnesium, Aluminium).
17. Subject is receiving an oral or intravenous immuno-suppressive therapy (e.g., inhaled steroids are not excluded) or has a known life-limiting immunosuppressive or autoimmune disease (e.g., human immunodeficiency virus, systemic lupus erythematosus) diabetes mellitus is not excluded).
18. Life expectancy less than 1 year.
19. Subjects under oral anticoagulation therapy (OAC) prior to implantation of DREAMS 3G unless DAPT can be maintained for a minimum of 6-month.  
  
Recommendation: If a subject requires OAC after DREAMS 3G implantation, DAPT should be maintained until 6 months follow up. Afterwards DAPT can be downsized to either ASA or Clopidogrel alone together with OAC for the remaining time period up to 12 months. After this, OAC monotherapy can be prescribed if still required.
20. Planned surgery or dental surgical procedure within 6 months after index procedure unless DAPT will be maintained.
21. In the investigators opinion subject will not be able to comply with the follow-up requirements.
22. Subject is currently participating in another study with an investigational device or an investigational drug and has not reached the primary endpoint yet.

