### 2.3 Device Description

DREAMS 3G is a scaffold system consisting of a balloon-expandable bioabsorbable scaffold pre-mounted on the balloon of a rapid-exchange PTCA catheter. The scaffold backbone is made from bioabsorbable Magnesium and contains two permanent x-ray markers made from Tantalum on the distal and on the proximal scaffold end, respectively. The surface of the scaffold backbone is completely coated with bioresorbable PLLA (Poly-L-Lactidic Acid) which incorporates Sirolimus. Sirolimus load is  $1.4 \pm 0.3 \mu\text{g}$  per  $\text{mm}^2$  scaffold surface.

The DREAMS 3G scaffold system is packaged in a dispenser. The dispenser is placed in an aluminium Tyvek pouch. The device is sterilized using ethylene oxide sterilization.

In vivo investigations using a porcine model show that DREAMS 3G provides vessel support for about 3-6 months and releases around 70% Sirolimus from the PLLA carrier during a period of 3 months after implantation.

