|                                                                                                                               | debris, thrombus)                                                                                                                           | for the other events prevalence not reported in literature) |            |
| Neurological events                                                                                                           | Permanent (stroke) or reversible (TIA) neurologic event, femoral nerve injury, peripheral nerve injury                                      | 0-0.5%                                                      | (82,104)   |
| Bleeding events                                                                                                               | Access site bleeding or hemorrhage, hemorrhage requiring transfusion or other treatment                                                     | 0.3-1.8%                                                    | (99)       |
| Allergic reactions                                                                                                            | To contrast media, tantalum, aluminium, anti-platelets, anticoagulants, to the drug carrier PLLA, to Sirolimus (derivates or similar drugs) | <1.0%                                                       | (139)      |
| Allergic reactions                                                                                                            | Magnesium and aluminium                                                                                                                     | Estimated <1%                                               | (140)**    |
| Infection and sepsis                                                                                                          |                                                                                                                                             | <1.0%                                                       | ***        |
| Death                                                                                                                         | All cause                                                                                                                                   | 0-1.7%                                                      | (24,95)    |

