\* The sum of all scaffold system events that have occurred are considered as device failure rate

\*\* Allergic reactions against magnesium are generally very rare and were not observed in previous studies with the Magmaris scaffold. There is no data published regarding implants containing aluminium. Generally, patients who develop problems after implantation of a metal

implant seem to have a higher in-vitro allergization against other metals (e.g. 52% of patients with a metal implant with a high allergization against nickel also developed an allergization against aluminium and vanadium (140). Allergic reactions against aluminium cannot be excluded but are estimated to occur with a frequency less than 1%.

\*\*\* No data published on infection and sepsis associated with a PTCA as it hardly occurs.

Potential adverse events related to sirolimus (following oral administration) include but are not limited to: Abnormal liver function, anemia, arthralgia, diarrhea, hypercholesterolemia, hypersensitivity, including anaphylactic/ anaphylactoid type reactions, hypertriglyceridemia, hypokalemia, infections, interstitial lung disease, leukopenia, lymphoma and other malignancies, thrombocytopenia. Appropriate contraindications and warnings are included in the IFU provided with the study device.

For all subjects, quantitative coronary angiography including IVUS and OCT will be performed at 6 and 12 months follow-up. Coronary angiography, IVUS and OCT are common medical tests. They rarely cause serious problems. However, complications can occur and include, but are not limited to:

- Bleeding, infection, and pain at the catheter insertion site
- Damage to blood vessels (including dissections)
- Allergic reaction to contrast media or medication

Other, less common complications include: arrhythmias, kidney damage, blot clots that can trigger a stroke, heart attack, or other serious problems, low blood pressure, pericardial effusion

The vasomotion test involves an infusion of acetylcholine, which can provoke a pathological narrowing of the vessel, which in turn may lead to chest pain, reduced blood supply to the heart, cardiac arrhythmia or an occlusion of the blood vessel. As the vasomotion test is performed during the coronary angiography, these side effects are generally easily controlled.

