#### Enrolled:

Provisionally enrolled subjects who met all eligibility criteria are considered enrolled. Enrolled subjects will be followed in accordance with the clinical investigation plan.

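### Exclusion 16 specifies the scaffold material as magnesium and aluminium only, although the protocol also describes tantalum markers and a PLLA coating and lists both as possible allergens

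*Protocol*

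**What the plan says.** Exclusion 16 lists known allergies or intolerances that rule a subject out: acetylsalicylic acid, P2Y12 inhibitors, heparin, contrast medium, then "Sirolimus, or similar drugs; or the scaffold material (Magnesium, Aluminium". The synopsis has the same text.

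Section 2.3 says that the backbone "contains two permanent x-ray markers made from Tantalum on the distal and on the proximal scaffold end". On the coating it says: "The surface of the scaffold backbone is completely coated with bioresorbable PLLA (Poly-L-Lactidic Acid) which incorporates Sirolimus".

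Table 3 in section 3.1 covers adverse events that can occur when the device is used as intended. Its first row on allergic reactions reads: "To contrast media, tantalum, aluminium, anti-platelets, anticoagulants, to the drug carrier PLLA, to Sirolimus (derivates or similar drugs", with a frequency below 1.0%. A second row covers magnesium and aluminium, with an estimated frequency below 1%.

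The status definitions in section 5.1 state: "Provisionally enrolled subjects who met all eligibility criteria are considered enrolled". In section 3.1, the paragraph on adverse events of oral sirolimus closes with: "Appropriate contraindications and warnings are included in the IFU provided with the study device".

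**The concern.** The protocol has two lists that bear on the same question. Table 3 says which materials may cause an allergic reaction. Exclusion 16 says which known allergies keep a subject out. The second list is shorter than the first, and the two missing items are both parts of the implant.

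At stake is the safety of a rare subject in a first-in-man study. Someone with a documented allergy to tantalum or PLLA could pass screening on the written criteria. The enrolment would also not show up as a breach of eligibility, because section 8.6.1 counts violations of relevant inclusion or exclusion criteria and none would have been violated. Of the two materials, tantalum is the one that section 2.3 calls permanent.

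**Working it through.** No arithmetic applies, and the plan states no figure to reproduce. The check sets the device description, the risk table and the criterion side by side.

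| Agent | Part of the implant? | Table 3, allergic reactions | Exclusion 16 |
|---|---|---|---|
| Magnesium | Yes, backbone (2.3) | Listed | Named |
| Aluminium | Yes, in the alloy (3.2) | Listed | Named |
| Sirolimus | Yes, in the coating (2.3) | Listed | Named |
| PLLA | Yes, coating (2.3) | Listed | Not named |
| Tantalum | Yes, markers (2.3) | Listed | Not named |
| Contrast media | No | Listed | Named |
| Anti-platelets | No | Listed | Covered by acetylsalicylic acid and P2Y12 inhibitors |
| Anticoagulants | No | Listed | Covered in substance by heparin |

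Every agent in Table 3 has a counterpart in exclusion 16 except PLLA and tantalum. Of the five implanted materials, three are named and two are not.

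Could another criterion catch them? None of the nine inclusion criteria and none of the other 21 exclusion criteria mentions tantalum, PLLA or device hypersensitivity in general.

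Is the bracket meant as a list of examples? Where the protocol gives examples, it usually marks them: exclusion 14 says that its list is not limiting, and exclusions 15 and 17 use *e.g.* The bracket in exclusion 16 has no such marker, so the natural reading is a closed list.

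From these steps and the enrolment definition in section 5.1, a subject whose only relevant history is a known tantalum or PLLA allergy meets the written criteria.

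**The case against.** The strongest reply is that exclusion 16 is not the only safeguard. Section 2.9 requires labels or manuals to carry all relevant contraindications, section 2.4 refers to the IFU for use of the device, section 5.9.2 asks for implantation in line with it, and sections 2.5 and 5.9 require implanters to be trained on it. If the IFU contraindicates allergy to any component, the gap may have no practical effect. This stands as a limit on the consequence. A reader might infer that sites would in fact enrol such patients; the documents do not show that, because the IFU is not available. They equally do not show that the IFU closes the gap, and the sentence in section 3.1 that points to it sits in a paragraph about sirolimus.

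A second reply is that the operative words are the scaffold material, and section 2.3 places the tantalum markers on the backbone itself, so an investigator might read the term broadly. That is possible, and the drafting of the lists is loose elsewhere: in exclusion 17 the *e.g.* introduces something that is not excluded. But a criterion that depends on a broad reading of a bracket naming two metals is at best ambiguous.

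A third reply is that Table 3 lists possible events for a class of procedures and does not say that each agent must be an exclusion. Also, section 1.1.3 says that the same coating is used in a stent marketed since 2011. Both points are fair. They could be grounds for leaving the two materials out on purpose, but the protocol gives no such reason.

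**Conclusion.** The mismatch is in the current text and holds in both places where exclusion 16 appears. It is minor. No endpoint, sample size, power or analysis is touched. The conclusion rests on reading the bracket as a closed list, and its practical weight depends on an IFU that is not shown.

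The size cannot be calculated from the documents. A reader might multiply Table 3's frequency by the planned enrolment to get a count of affected subjects. That is not supported: the figure is the frequency of reactions, pooled over contrast media, anti-platelets, anticoagulants, sirolimus, aluminium, tantalum and PLLA. It is not the share of candidates with a known tantalum or PLLA allergy, which is the only group that the criterion could affect. That group is probably very small.

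Two other inferences should be avoided. Permanent exposure applies to tantalum only, since section 2.3 describes the PLLA as bioresorbable. And the sirolimus release described in section 2.3 says nothing about PLLA allergy: it comes from a porcine model, and sirolimus allergy is already an exclusion.

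**What to change.** Reconcile exclusion 16, in the synopsis and in section 4.10, with section 2.3, Table 3 and the IFU. There are two ways to do this: make the bracket cover all implanted component materials that the protocol itself names as allergens, or state why tantalum and PLLA are deliberately left out. Which of the two is right is for the sponsor to decide; this review does not propose the clinical rule. Whatever is chosen, the synopsis, section 4.10 and the eligibility page of the eCRF should agree, and the protocol should not be narrower than the IFU without saying so.

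The cost is a minor wording change in two places and a matching eCRF edit, made with the next amendment.
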